### Data analyses

The primary analysis will involve a comparison of the mean WOSI scores between the two surgical treatment groups on an intention-to-treat basis. This analysis is a two-sample independent t-test to assess whether there is a statistically significant difference between groups for the mean WOSI score at 2 years. The 5% significance level will be employed. The underlying assumption for the WOSI data is that a normal distribution will exist, but if the sample distribution is determined to depart from normal, then a Wilcoxon rank sum test will be performed. In addition, a Generalized Estimated Equations (GEE) [70] analysis will be conducted to determine whether there is an effect over time (repeated measures) (i.e. 3, 6, 12 months and 2 year follow-ups).

The planned secondary analyses are performed using a 5% significance level. No p-value adjustment is required for multiple outcomes, as treatment effectiveness is based only on the primary variable (i.e. WOSI score). Secondary outcome measurements will be analyzed in the following manner: 1) The ASES scores and Constant Scores using t-tests and GEE analysis in a similar fashion to the primary outcome; 2) Recurrence rates will be compared between treatment groups using a Fisher's exact test; and, 3) Operative times between the two treatment groups will be compared using a logarithmic scale and a t-test.

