**Methods:**

This study is a multi-centre randomized clinical trial with a calculated sample size of 58 patients (p = 0.05, 80% power). Eligible patients are clinically diagnosed with MDI or MDL-AII and have failed standardized non-operative management. A diagnostic shoulder arthroscopy is performed to confirm eligibility, followed by intra-operative randomization to the ETAC or ICS surgical procedure. The primary outcome is the disease-specific quality of life questionnaire (Western Ontario Shoulder Instability Index), measured at baseline, 3, 6, 12 and 24 months. Secondary outcomes include shoulder-specific measures (American Shoulder and Elbow Surgeons Score and Constant Score). Other outcomes include recurrent instability, complications and operative time.

The outcome measurements will be compared on an intention-to-treat basis, using two-sample independent t-tests to assess statistical significance. A Generalized Estimated Equations (GEE) analysis will determine whether there is an effect over time.

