#### Randomization

Consenting patients, clinically diagnosed with either MDI or MDL-AII, and who have failed non-operative rehabilitative management, are randomized to either an ETAC or open ICS surgical treatment. Computer-generated (STATA 8.2, StataCorp, USA), stratified block randomization is used to ensure that imbalances between group assignments do not occur during the course of the trial. Stratification is based on two variables: 1) surgeon – to account for any differences between surgeons, and, 2) diagnosis (MDI and MDL-AII) – to account for any differences in the severity of pathology. Thus, the stratification process results in a separate set of sealed numbered opaque envelopes for each participating surgeon and for each type of shoulder instability (MDI or MDL-AII).

Randomization occurs in the operating room following a diagnostic arthroscopy. Once the surgeon confirms that the patient meets the eligibility criteria, the next consecutive envelope is opened by the study research coordinator or the assigned circulating nurse, which randomly allocates the patient to either open ICS or ETAC treatment. If the patient is ineligible, the surgeon performs the most appropriate procedure as he/she sees fit.

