#### Sample size

The sample size calculation is based on the existing baseline information from the first thirty patients entered into the trial. The first 30 patients had a mean WOSI score of 1461.68 with a normal distribution of the data and a standard deviation of 364.52. The estimated minimal clinically important difference between treatment groups is 20%.

Sample size parameters:

▪ Comparing 2 independent group means with a MCID between means = 20%

▪ Mean group 1 = 1461.68; Mean group 2 = 1169.34; Standard Deviation (SD) = 364.52

▪ Predicted patient drop-out rate (based on drop-out rate to date) = 12%

Using these sample size parameters, an alpha value p = 0.05, and 80% power, the calculated sample size is 29 patients per group (Table 1).

**Table 1 T1:** Sample size calculation for the required number of subjects in each treatment group (double sided).

**Alpha level("p" value)**	**Power**			
	**60%**	**70%**	**80%**	**90%**

0.10	12	15	20	27
0.05	16	20	**25***	33
0.01	25	30	37	47
0.001	40	46	54	65

N per group = 25* Expected dropout 12% 25/.88 = 28.4 Total per group 29 Grand Total **58 patients**

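### The primary t-test uses neither baseline WOSI nor the two stratification factors: it is valid, but gives up precision the trial could have at almost no cost

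*Protocol article*

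**What the plan says.** Under Data analyses, the primary comparison is by intention to treat and is a "two-sample independent t-test to assess whether there is a statistically significant difference between groups for the mean WOSI score at 2 years". If the scores are not normally distributed, "then a Wilcoxon rank sum test will be performed"; that fallback is also unadjusted and unstratified. As an addition, a "Generalized Estimated Equations (GEE) [70] analysis will be conducted to determine whether there is an effect over time". The visits listed for it are all post-operative and no covariates are named. ASES and Constant scores are to be handled in the same way.

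The Abstract (Methods) says that WOSI is "measured at baseline, 3, 6, 12 and 24 months", so a pre-operative value is part of the schedule. Under Randomization: "Stratification is based on two variables: 1) surgeon", the second variable being diagnosis. This produces "a separate set of sealed numbered opaque envelopes for each participating surgeon and for each type of shoulder instability". The stated purpose is to allow for possible differences between surgeons and in severity of pathology.

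No section of the article mentions adjustment for baseline WOSI, surgeon or diagnosis.

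**The concern.** The design treats surgeon and diagnosis as factors that might matter, and it measures the primary outcome before surgery. The primary analysis then uses none of this. Two separate costs can follow.

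- **Baseline WOSI.** If the pre-operative score predicts the 24-month score, an unadjusted comparison carries residual variance that a linear model would remove. The t-test's standard error remains correct; it is just larger than it need be.
- **Strata.** Blocked allocation within strata removes between-stratum variation from the true sampling error of the treatment difference. A two-sample t-test still counts that variation as error. If the strata are prognostic, the reported standard error is too large.

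Both costs point towards missing a real difference. The trial planned 58 patients, had enrolled 49 between 1999 and 2005, and is meant to settle whether ETAC is recommended or abandoned.

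**Working it through.** **Inputs from the Sample size section.** Means 1461.68 and 1169.34, difference 292.34, SD 364.52, dropout 12%. The error rates are given as "an alpha value p = 0.05, and 80% power, the calculated sample size is 29 patients per group", and Table 1 is marked double sided. The SD comes from baseline scores of the first 30 patients, so it is an unadjusted SD, used here as in the plan for the 24-month score.

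**Step 1: reproduce the plan's figure.**
- d = 292.34 / 364.52 = 0.802.
- n per group = 2 × (1.960 + 0.842)² / 0.802² = 24.4, rounded up to 25.
- 25 / 0.88 = 28.4, rounded up to 29 per group, 58 in total.

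The plan's figure reproduces. Power at 25 per group is 80.9% by the normal approximation and 79.3% by the noncentral t. The trial is therefore sized for the unadjusted test, and that test delivers what was planned.

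**Step 2: baseline adjustment.** The baseline to 24-month correlation r is not in the documents and is an assumption. Adjustment multiplies the residual SD by √(1 − r²), so the effective d is 0.802 / √(1 − r²). Power comes from a noncentral t with noncentrality d × √(n/2), two-sided 0.05, and one degree of freedom spent on baseline.

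| r | effective d | power, 25 per group |
|---|---|---|
| unadjusted | 0.802 | 79% |
| 0.1 | 0.806 | 80% |
| 0.2 | 0.819 | 81% |
| 0.3 | 0.841 | 83% |
| 0.4 | 0.875 | 86% |
| 0.5 | 0.926 | 89% |

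These figures are for baseline only. Spending about six degrees of freedom on further terms costs about 0.2 points.

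**Step 3: if enrolment stopped at 49.** 49 × 0.88 = 43.1, or about 43 evaluable. Power is 73% unadjusted, 77% at r = 0.3, 80% at r = 0.4 and 84% at r = 0.5.

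**Step 4: dependence on the target difference.** The sample size uses 292.34 / 21 = 13.9 points on the 0–100 scale, with SD 364.52 / 21 = 17.4. The MCID section sets 20 points. At 20 points the unadjusted test has 97.9% power with 25 per group, and baseline adjustment at r = 0.3 adds about 1 point.

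**Step 5: the strata.** This was simulated with 50 patients, blocks of 4, either 4 or 8 surgeons by 2 diagnoses, and 3,000 replicates per setting. The number of surgeons, the block size and the between-stratum share of variance are assumptions.
- No between-stratum variance: the t-test's standard error is correct and type I error is about 5%.
- 20–30% of variance between strata: the mean reported standard error is about 0.28 SD against a true value of 0.24–0.26 SD, an overstatement of roughly 7–15%. Type I error is about 3%; with strata in the model it is about 4–5%.
- 8 surgeons, no stratum effect, and every surgeon-by-diagnosis cell as a separate term: power falls to 73%, against 79% unadjusted. The form of the adjustment matters.

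**The case against.** The strongest reply is that nothing here is an error. The t-test is unbiased under randomization, the sample size was computed for that test, and the stated power is delivered. This stands: the loss is measured against a better analysis, not against the plan's own promise.

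A second reply is that the benefit rests on a correlation nobody has reported. Baseline precedes surgery and the outcome follows it by two years, so r could be low; at 0.2 the gain is under 2 points. This also stands, which is why the range begins at 0.1. The benefit shrinks further if 20 points is the relevant difference.

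A third is that stratifying to allow for possible differences does not predict that there are any. That is fair, so the statement about the standard error has to be conditional.

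Chance baseline imbalance adds no separate harm. A 5-point imbalance at r = 0.4 with equal SDs would move the unadjusted difference by about 2 points, but 5 points is about one standard error (17.4 × √(2/25) = 4.9), and the t-test's standard error already covers such variation.

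The point cannot be set aside as a detail for an unseen analysis plan. The article names the primary test outright, and the additional GEE names no covariates.

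**Conclusion.** The point holds as a recommendation on efficiency. The primary analysis leaves available precision unused. At the design effect with 25 per group, the gain from baseline adjustment runs from under 1 point of power at r = 0.1 to about 10 points at r = 0.5. With about 43 evaluable patients it is about 4 points at r = 0.3 and 11 at r = 0.5. These figures assume the plan's SD applies at 24 months and depend on an r the documents do not give. Any overstatement of the standard error depends on surgeon or diagnosis predicting outcome.

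A reader might infer three stronger things, and the documents support none of them:

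- That the test is invalid or produces excess false positives. Any error in the standard error is on the conservative side, and omitting baseline does not invalidate it.
- That the trial is underpowered for its stated analysis. The 58 patients give about 80%.
- That the recruitment target is out of reach. The Discussion reports slow enrolment, 49 of 58, in a trial that is still running.

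**What to change.** Before outcome data are examined by arm, amend the primary analysis to a linear model of 24-month WOSI on arm, baseline WOSI, diagnosis as a main effect, and surgeon. Pool low-volume surgeons or fit surgeon as a random intercept; do not fit the full set of surgeon-by-diagnosis cells. Report the adjusted mean difference in points with its 95% confidence interval. Keep the t-test as a supportive analysis. Use the same model for ASES and Constant scores where a baseline value is available.

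The cost is a few degrees of freedom and a documented, dated amendment. The documentation matters because 49 patients are already enrolled and surgeons and patients know the allocation. No new data are needed.

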### Data safety monitoring committee and trial steering committee

The Trial Steering Committee (TSC) has 4 members with backgrounds in epidemiology, clinical trial methodology and orthopaedic surgery. The duties of this committee are to conduct and manage the trial, review recruitment rates and overall compliance with data collection and study protocol.

The Data Safety Monitoring Committee (DSMC) monitors all adverse events and major complications that occur throughout this trial. The Committee is formed by 4 independent members who are neither investigators nor collaborators in this trial. Their backgrounds include orthopaedic surgery, joint injury and arthritis research, sport medicine and epidemiology.

The DSMC provides an advisory role to the Trial Steering Committee and is not involved in conducting or managing the trial. The DSMC meets annually to review recruitment reports and overall compliance with data collection and study protocol, and subsequently provides feedback and recommendations to the TSC.

In the event of a major complication, the DSMC members hold an emergency meeting to review of the operative report and patient chart, and determine whether the complication could occur with greater incidence in one intervention compared to the other. To prevent a biased evaluation, the group is blinded to treatment allocation. The DSMC then provides an immediate recommendation for the TSC to decide whether the event is serious enough to warrant stopping the trial. The TSC will weigh the benefits of the interventions and the risks of potential adverse events to collectively decide on the continuation or discontinuation of the clinical trial.

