Another secondary outcome is the Constant Score adopted by the European Shoulder Society for overall clinical functional assessment of the shoulder [54]. The Constant Score records a variety of shoulder measurements, including an objective test of strength using a spring-loaded measuring device. The Constant Score is based on a 100-point scoring system calculated from a self-assessment portion that evaluates pain and ability to perform tasks of daily living, and a clinical assessment portion that tests shoulder strength and active range of motion. A higher score reflects a better outcome.

Additional outcomes include the documentation of recurrent instability, complications and operative time. Recurrent instability is defined as a self-report of one or both of the following criteria: a) A minimum of two subluxation events, where subluxation is defined as the symptomatic translation of the humeral head relative to the glenoid articular surface [58]; and/or, b) At least one re-dislocation, where dislocation is defined as an increased motion of the humeral head relative to the glenoid to the point of complete separation of articular surfaces [58].

The outcome measures are collected at each clinical follow-up appointment in a standardized fashion and by a trained independent assessor who is blinded to treatment status. If patients do not return to the clinic or miss an appointment, all attempts are made to have the questionnaires completed through mail-out or internet-based formats.

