### Safety considerations of open ICS and ETAC

Serious adverse events are reported to the trial's Data Safety Monitoring Committee (DSMC), where the committee is blinded to the treatment allocation. The most common potential complication with open ICS and ETAC surgery is a stiff shoulder, or adhesive capsulitis. This complication can be observed at similar rates with various types of surgical shoulder procedures. In this trial to date, two cases of adhesive capsulitis have been observed. However, the DSMC determined that the complications did not occur with a greater incidence in one intervention compared to the other. The Trial Steering Committee agreed that the events were not serious enough to warrant stopping the trial.

Transient sensory abnormalities, which are common events with shoulder procedures and usually resolve, have not been observed in this trial to date. There is one potential complication that is unique to the thermal procedure, which is catastrophic capsular loss secondary to capsule dissolution. Capsule dissolution has not been observed in either the pilot trial or in this randomized clinical trial.

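### The DSMC is said to be blinded to allocation, reads records that would normally reveal it, and is reported to have compared complications by arm; these statements cannot all hold

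*Protocol article*

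**What the plan says.** The section on the two trial committees (Methods) gives the DSMC its procedure for a major complication. First the source material: "the DSMC members hold an emergency meeting to review of the operative report and patient chart". Then the question it must answer from that material: "determine whether the complication could occur with greater incidence in one intervention compared to the other". The sentence that follows sets the condition: "To prevent a biased evaluation, the group is blinded to treatment allocation". The DSMC then advises the TSC, which decides whether the trial continues.

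The safety section of the Discussion says again that "the committee is blinded to the treatment allocation". It reports that "two cases of adhesive capsulitis have been observed", and that "the DSMC determined that the complications did not occur with a greater incidence in one intervention compared to the other". The TSC is then said to have judged the events not serious enough to stop the trial. The same section adds: "There is one potential complication that is unique to the thermal procedure, which is catastrophic capsular loss".

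Under Outcome measures, complications are also a recorded trial outcome: "Additional outcomes include the documentation of recurrent instability, complications and operative time". The Data analyses section names between-arm tests for recurrence and operative time, but none for complications.

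**The concern.** A comparison of incidence between two arms needs each event assigned to its arm. A committee without allocation cannot do that. Yet the article gives the DSMC this task and reports that it has been carried out, while saying twice that the committee is blinded.

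The records it is told to read make matters worse. The article's own descriptions of the two procedures differ at every step: one is an open deltopectoral approach with the subscapularis and capsule incised, the other a heat probe passed through arthroscopic portals. An operative report would normally show which was done.

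At stake is whether the independent body can see an excess of harm in one arm, and what a reader may take from the reassurance already given about the two cases.

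**Working it through.** The plan gives no figure for this comparison, so there is none to reproduce. The main check is to set the statements side by side; a short calculation then shows how much two events can say.

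**Consistency of the text**

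1. *Task.* The Methods ask whether a complication could be more frequent with one intervention. Taken alone, this might mean clinical plausibility. The Discussion, however, reports that the complications were not in fact more frequent with one intervention, which is a statement about observed events by arm.
2. *Blinding.* Both sections state it. Neither describes coded arms, redacted records or an unblinded statistician.
3. *Source material.* The committee reads the operative report and the chart. In the Blinding section, by contrast, the outcome assessor is denied the chart.
4. *The two branches.* If the blinding holds, events cannot be assigned to arms and the reported determination has no stated basis. If the records are read unredacted, events can be assigned, but the blinding does not hold. Coded A/B labels alone would not rescue the text, because one labelled case read beside its operative report would decode them.

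**What two events can show**

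Inputs: two adhesive capsulitis cases (Discussion, safety section) and 49 patients enrolled (Discussion, enrolment section). The split by arm is not in the text at hand, so 25/24 is assumed, with 25/25 and the planned 29/29 as alternatives.

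Under equal risk, the probability that both events fall in the same arm, whichever arm it is, is

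P = [n1(n1 − 1) + n2(n2 − 1)] / [N(N − 1)].

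- 25/24: (25×24 + 24×23) / (49×48) = (600 + 552) / 2352 = 0.490
- 25/25: 2×(25×24) / (50×49) = 1200 / 2450 = 0.490
- 29/29: 2×(29×28) / (58×57) = 1624 / 3306 = 0.491

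The two-sided Fisher's exact test agrees. At 25/24, a 1-1 split gives p = 1.00. A 2-0 split gives p = 0.49 if both events are in the arm of 25, and p = 0.23 if both are in the arm of 24. At 29/29, a 2-0 split gives p = 0.49.

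A blinded committee cannot tell 2-0 from 1-1. An unblinded one could tell them apart, but neither split would show a difference or exclude one. The Discussion's unqualified sentence therefore claims more than two events can support, whatever the committee saw.

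**The case against.** The strongest reply is that nothing is impossible here. If the operative report reveals the arm, the DSMC can make the comparison and only the blinding fails. Masking a monitoring committee is a deliberate choice with a stated reason, and the mechanics usually sit in a charter that a journal article omits. This stands in part: the text does not show that the comparison could not be made, only that it could not be made while the stated blinding holds. It does not remove the conflict, because the article itself asserts the blinding, the revealing records and the completed comparison together.

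Several stronger readings are tempting and are not supported:

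- *That this is the trial's only safety comparison, or that harms are never tabulated by arm.* Complications are a recorded outcome, recurrence is tested between arms, and the DSMC is said to monitor all adverse events. A final comparison of complications may be set out in documents not shown. What can be said is that this is the only between-arm comparison of complications the article describes, and that the listed content of the annual DSMC meeting is recruitment and compliance.
- *That the decision to continue rests on an invalid comparison.* The ground stated for the TSC's decision is that the events were not serious enough, and the TSC is not described as blinded.
- *That the blinding would hide the complication unique to the thermal procedure.* Such an event identifies its own arm, so it is the one least hidden. The article says that capsule dissolution has not been observed.

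It is also fair to say that two events would have been uninformative with allocation known. That counts against the wording of the reported determination as much as against the blinding.

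**Conclusion.** The concern holds in this form: the blinding, the review of operative reports and charts, and the reported between-arm determination are mutually inconsistent as written. Followed to the letter, the plan leaves the DSMC either unable to compare complications by arm or blinded in name only. The documents do not show which of these happened, nor that the determination about the two cases was wrong, only that its basis is not given.

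The consequence is for safety oversight. The primary analysis of the Western Ontario Shoulder Instability Index and the sample size are unaffected. As to size, with about 25 patients per arm a 2-0 split in one direction or the other has about a 49% probability under equal risk. This assumes near-equal allocation, since the arm totals are not in the text at hand. The textual conflict itself depends on one ordinary assumption, that an unredacted operative report shows whether the procedure was open or thermal.

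**What to change.** Reconcile the committee section with the safety section of the Discussion.

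1. Replace the blinding sentence in the committee section, and its repetition in the Discussion, with a statement that the independent DSMC receives a short closed table of complications by arm, with the number of patients in each arm, at its annual and emergency meetings. The TSC receives pooled data and the DSMC's recommendation.
2. State the basis of the determination on the two adhesive capsulitis cases, that is, what the DSMC saw and how events were assigned to arms. Otherwise, reword it to say that two events are too few to show or exclude a difference between the operations.

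The cost is a change of wording in the protocol and in any DSMC charter, and one short table prepared by someone outside the TSC. The downside is that four independent members see safety data by arm, so the protection from bias that the present sentence seeks is given up for that group. They are neither investigators nor collaborators and do not run the trial, so the loss is small. On pooled data the TSC would depend on the DSMC's recommendation when it weighs risks against benefits, and the text should say so.
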